## Abstract

**Background:**

Psychotherapy is central to the treatment of mental disorders, highlighting the importance of medical students and residents developing competencies in this area. Chinese medical residents have expressed a strong need for psychotherapy training, yet they are generally dissatisfied with the current offerings. This paper presents the protocol for an evidence-based, well-structured psychotherapy teaching program aimed at medical students and residents.

**Objective:**

This study involves a randomized controlled trial of a 2-day multimodal intensive educational intervention designed to evaluate the effectiveness of a new psychotherapy teaching program for medical students and residents in China. The primary outcomes include participants’ knowledge and utilization of psychotherapy, training program acceptability, self-reported self-efficacy, and motivation to apply psychotherapy.

**Methods:**

This 2-arm randomized controlled trial was conducted at Sir Run Run Shaw Hospital. The study aimed to recruit approximately 160 medical students and residents, with about 80 participants in the intervention group and 80 in the control group. Both groups completed a baseline survey before participation, reporting their psychotherapy knowledge, utilization of psychotherapy, self-efficacy, and self-motivation. The intervention group received a 2-day multimodal intensive educational intervention (supervision-based online teaching), while the waitlist control group did not receive any intervention during this period. Both groups were followed up for 8 weeks, completing the same survey administered at baseline. At the end of the study, the control group received the intervention. The primary outcome measure was the change in trainees’ psychotherapy knowledge before and after the intervention training. Secondary outcome measures included changes in the trainees’ utilization of psychotherapy, self-reported self-efficacy, and self-reported motivation for psychotherapy. Additionally, training program acceptability was assessed. Analysis of covariance was used to analyze the primary outcomes. Pearson correlations and regression analysis explored factors associated with the knowledge score at baseline. The secondary outcomes, including participants’ psychotherapy utilization, confidence, and motivation, were analyzed using the same methods as for knowledge. All tests were 2-tailed, with a significance level set at *P*<.05.

**Results:**

A total of 160 participants were recruited and randomized between January 4 and 12, 2024. Baseline assessments were conducted from January 28 to February 1, 2024. The psychotherapy training program for the intervention group took place on February 3 and 4, 2024. Posttraining assessments were conducted starting April 1, 2024. Due to withdrawals, incomplete surveys, and data loss, we had a total of 113 participants: 57 in the intervention group and 56 in the control group. The amount of data varied across measures. The data analysis was finished in August 2024.

**Conclusions:**

This study aims to evaluate the effectiveness of the multimodal psychotherapy training program for medical students in China. If this brief, cognitive behavioral therapy–based psychotherapy skill training proves effective, the potential mental health impact of its nationwide expansion could be significant.

**Trial Registration:**

ClinicalTrials.gov NCT06258460; https://clinicaltrials.gov/ct2/show/NCT06258460

**International Registered Report Identifier (IRRID):**

DERR1-10.2196/58037

## Introduction

### Background

The delivery of psychosocial and psychotherapeutic interventions remains central to the treatment of many patients with psychiatric disorders (eg, obsessive-compulsive disorder, panic disorder, major depression, eating disorders, and addictive behaviors) and psychosomatic disorders (eg, hypertension, bronchial asthma, and rheumatoid arthritis) [1,2]. Cuijpers et al [3] conducted a large-scale network meta-analysis to examine the effects of various types of psychotherapies for adult depression, including cognitive behavioral therapy (CBT), interpersonal therapy, psychodynamic therapy, problem-solving therapy, behavioral activation, life-review therapy, and “third-wave” therapies, as well as nondirective supportive counseling. They found that all types of these therapies were more effective than care-as-usual and waiting list control conditions and that most therapies were more efficacious than placebo. Additionally, most therapies maintained significant effects at the 12-month follow-up compared with care-as-usual. A strong evidence base indicated that several psychotherapy modalities were effective for most mental disorders, whether used alone or in combination, primarily including behavior therapy, CBT, and interpersonal psychotherapy [4,5]. According to a systematic review and meta-analysis, the emotional change processes and mechanisms of psychotherapy were most strongly associated with specific CBT methods, such as fear habituation, emotion regulation and experience, and the habitual reorganization of maladaptive emotional perceptions [6]. Today, CBT is recommended as a first-line intervention for both the acute treatment and relapse prevention of various mental illnesses, including major depressive disorder, and most patients prefer psychological treatment over pharmacologic options [5]. Therefore, medical students in clinical rotations and residents working in psychiatric and psychosomatic departments should be required to develop competencies in psychotherapy, particularly in CBT [7]. However, there remains a significant treatment gap for mental disorders in China [8]. Despite the high prevalence of mental disorders in the country, medical professionals in psychiatric or mental health departments often have a comparatively low capacity to provide adequate care and lack qualified training in psychotherapy. Learning basic psychotherapy skills would benefit medical students, residents, and other health care providers (HCPs), including doctors and nurses, across all departments. These skills can be applied in clinical practice to enhance doctor-patient relationships [9]. A study conducted in Beijing found that after participating in a 2-year psychotherapy training program, medical doctors reported improvements in diagnosing and treating mental illness, as well as in doctor-patient communication and the development of strong doctor-patient relationships. Patients also demonstrated significant improvements in levels of depression and anxiety, the severity of physical symptoms, quality of life, and the patient-rated therapeutic relationship [9]. Therefore, psychotherapy training for medical students, residents, and other HCPs requires greater emphasis.

A narrative review indicated that medical residents in psychiatry have a strong need for psychotherapy training to enhance their competence, yet they generally express dissatisfaction with the current training programs [10]. Therefore, providing evidence-based and well-designed psychotherapy training programs is essential for equipping medical students and residents with a foundational understanding of psychotherapy and the necessary skills for clinical practice [11]. Compared with traditional methods, psychotherapy teaching that emphasizes skill practice and role experience is more popular and effective. For instance, a single-day simulation training program has proven effective in psychiatry for medical students, enhancing their knowledge, communication and interview skills with patients, and confidence in treatment [12]. Despite the critical importance of learning psychotherapy skills during medical school and residency, there is a notable lack of formal evaluation of psychotherapy teaching methods and their efficacy. Given the lack of access to psychotherapy, medical and psychological educators, along with program directors, should design high-quality curricula to teach medical students, residents, and other HCPs the essential knowledge and skills in psychotherapy. These curricula should be evaluated through well-conducted, methodologically robust randomized controlled trials (RCTs) [13].

### Aim and Hypotheses

To evaluate the effectiveness of the multimodal psychotherapy training program for medical students in China, well-designed RCTs of psychotherapy teaching programs are urgently needed. The primary aim of this proposed project is to assess the effectiveness of a new multimodal psychotherapy teaching program for medical students and residents in China, which is designed to enhance their psychotherapeutic skills and improve their performance in entry-level clinical settings. The primary hypothesis was that, compared with a control intervention, the intervention group receiving the psychotherapy teaching program would acquire significantly more knowledge about psychotherapy after training. We also hypothesized that the program would lead to an increase in the utilization of psychotherapy and be associated with improved knowledge in this area. The third hypothesis posited that trainees’ self-reported self-efficacy and motivation to apply psychotherapy in clinical practice would increase significantly.

## Methods

### Patient and Public Involvement

Neither participants nor the public were involved in the trial’s design, recruitment, or conduct of this study.

### Study Design and Participants

This study was an RCT of a 2-day multimodal intensive educational intervention aimed at enhancing the clinical skills in psychotherapy of Chinese medical students and residents. The trial included a waitlist control group, with 8 weeks of follow-up for all participants. A detailed schedule of the study procedures is summarized in Figure 1.

**Figure 1 figure1:**
[figure not shown]
Flowchart study design.

Study participants (n=160) primarily included medical students, residents, and a few other HCPs, such as doctors and nurses, in China. There were no specific restrictions for participants, although most were from Zhejiang University School of Medicine. An overview of participant eligibility criteria is provided in Textbox 1.

Study inclusion criteria (participants who did not qualify for the criteria were not recruited to participate in this study).Medical students, residents, and other health care providersAged 18 years or olderExpressing an interest in psychotherapyWilling to receive randomizationWilling to provide informed consent to participate in the study

### Sample Size and Power Calculation

The sample size was calculated based on the primary outcome using G*Power [14] (version 3; Universität Düsseldorf). As the data were continuous variables and analysis of covariance (ANCOVA) would be used to compare differences between the 2 groups, an a priori analysis selecting ANCOVA as the statistical test was conducted to determine the required sample size. As only a few studies have examined the effectiveness of psychotherapy training for medical students, we were unable to reference effect size or other data as criteria. Therefore, a medium effect size for the primary outcome was estimated preliminarily. It was determined that 128 participants (64 in each group) would be required to achieve 80% power (effect size *f*=0.25; 1 – β=0.80; α=.05). To account for potential attrition, we aimed to recruit approximately 160 participants (80 in each group), ensuring that the proposed analysis would be sufficiently powered even if 25% of participants in each group were lost to attrition.

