### Data Analysis

All data were automatically collected via WenJuanXing through a WeChat-based link. The data were downloaded from the WenJuanXing database into a user-specific Excel file. This study did not include interim analyses; data were analyzed only after all had been collected. The trial statistician blinded the intervention assignment in the data using R software (R Foundation for Statistical Computing) and SPSS (2013 release; IBM Corp.).

The primary hypothesis was that, compared with the control intervention, the intervention group receiving the psychotherapy teaching program would significantly gain more knowledge about psychotherapy after training. We also hypothesized that the program would lead to increased utilization of psychotherapy and be associated with improvements in knowledge. The third hypothesis posited that trainees’ self-reported self-efficacy and motivation to apply psychotherapy in clinical practice would increase significantly.

Descriptive statistics were used to assess demographic and psychotherapy-related characteristics at baseline. Following normality and homogeneity of variance tests, ANCOVA was used to analyze the primary outcomes. In the ANCOVA model, the dependent variable was the change in the knowledge score. The fixed factor was the group (intervention group or control group), while the covariates included the mean score of psychotherapy knowledge at baseline and years of psychotherapy experience. Pearson correlations and regression analysis (both linear and binary regression models) were used to explore factors associated with the knowledge score at baseline and to assess the increase in psychotherapy utilization in both the intervention and control groups. The secondary outcomes—participants’ psychotherapy utilization, confidence, and motivation—will also be analyzed in the same manner as knowledge.

A complete case analysis was performed, excluding any participants with missing information on the posttraining assessment. Additionally, a sensitivity analysis of the missing data was conducted to determine whether the missingness is random. Demographic information and scores for psychotherapy knowledge, utilization, confidence, and motivation at baseline were compared between the complete data group and the missing data group. All tests were 2-tailed, with a significance level set at *P*<.05.

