## Results

This study recruited 160 participants from January 4 to January 12, 2024. The 2-day training program took place on February 3 and February 4, 2024, and the posttraining assessment was completed on April 1, 2024. Due to withdrawals, incomplete surveys, and data loss, we had a total of 113 participants: 57 in the intervention group and 56 in the control group. The amount of data varies for each measure. Data analysis was completed in August 2024. The results will be published in peer-reviewed journals. If found to be effective, the psychotherapy training program and the accompanying program booklet will be made freely available to the public by the end of the trial.

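### Recruiting 160 does not keep 80% power after 25% loss per group: 60 per group remain where the plan requires 64, so the target covers only 20% loss

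*Protocol article*

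**What the plan says.** The Sample Size and Power Calculation section bases the calculation on the primary outcome: "an a priori analysis selecting ANCOVA as the statistical test was conducted to determine the required sample size". The inputs are a medium effect, "effect size *f*=0.25", 80% power and alpha of .05. The result is: "It was determined that 128 participants (64 in each group) would be required to achieve 80% power". The target is then raised to about 160, 80 per group, with the stated aim of "ensuring that the proposed analysis would be sufficiently powered even if 25% of participants in each group were lost to attrition".

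The Data Analysis section fixes the rest of the setting. On sidedness: "All tests were 2-tailed, with a significance level set at" .05. On the model, "the covariates included the mean score of psychotherapy knowledge at baseline and years of psychotherapy experience", so there are two covariates. The analysis uses complete cases, leaving out anyone without the post-training assessment.

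The Results section reports that 160 were recruited and that "we had a total of 113 participants: 57 in the intervention group and 56 in the control group", and adds that the amount of data differs between measures.

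**The concern.** Two adjacent statements in the sample size section cannot both be true. One says 64 per group are needed for 80% power. The other says 80 per group are enough even if a quarter of each group is lost, yet a quarter of 80 is 20, which leaves 60. The only power criterion the article gives is 80%, so the phrase about sufficient power has to be read against it.

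The error bears on the primary analysis, because lost participants drop out of a complete-case ANCOVA and the article describes nothing that recovers the lost information. A reader who takes the attrition clause at face value would think the design had a 25% margin when it had 20%. Should the knowledge result be null, that reader would overrate the trial's ability to have detected f = 0.25.

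**Working it through.** **Inputs.** From Sample Size and Power Calculation: f = 0.25, power 80%, alpha .05, 128 required (64 per group), 160 recruited (80 per group), 25% attrition per group. From Randomization and Group Allocation: 1:1 allocation. From Data Analysis: two-sided tests, two covariates, complete cases. From Results: 113 participants (57 and 56).

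**Formula.** For the group effect in a two-group ANCOVA, power is the probability that a noncentral F variable exceeds the central F critical value at .05, with df1 = 1, df2 = N − 2 − (number of covariates) and noncentrality λ = f² × N = 0.0625 × N.

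**Step 1: reproduce the plan's figure.** The smallest N with at least 80% power is 128 with 0, 1 or 2 covariates. With two covariates, N = 127 gives 79.8% and N = 128 gives 80.1%. The stated 128 is therefore right.

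**Step 2: apply the stated attrition.** 80 × 0.75 = 60 per group and 160 × 0.75 = 120 in total. The shortfall against the requirement is 64 − 60 = 4 per group, 8 in total.

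**Step 3: power with two covariates.**

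| Analysed N | Loss from 160 | λ | df2 | Power at f = 0.25 | f detectable at 80% power |
|---|---|---|---|---|---|
| 128 | 20% | 8.00 | 124 | 80.1% | 0.25 |
| 120 | 25% | 7.50 | 116 | 77.5% | 0.258 |
| 113 | 29.4% | 7.06 | 109 | 75.0% | 0.266 |

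Dropping one or both covariates leaves these power figures unchanged to one decimal, apart from N = 128, which becomes 80.1% to 80.2% by rounding only.

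**Step 4: what 160 covers, and what 25% would need.** 160 × 0.80 = 128, so 160 covers exactly 20% loss. To keep 64 per group after 25% loss needs 64 / 0.75 = 85.3, that is 86 per group or 172 in total (128 / 0.75 = 170.7, or 171, if only the total is inflated). Note that 128 × 1.25 = 160. This suggests that the requirement was multiplied by 1 + 0.25 instead of divided by 1 − 0.25, but that is an inference; the article does not show the step.

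**Step 5: reported loss.** (160 − 113) / 160 = 47 / 160 = 29.4%, beyond both the claimed 25% and the true 20% margin.

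**Step 6: could another reading rescue the clause?** A one-sided alpha of .05 would give 85.9% power at 60 per group. It would also give 87.9% at 64 per group, so it does not reproduce 128, and it contradicts the two-tailed testing in Data Analysis.

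**The case against.** The arithmetic is hard to dispute; the case on the other side is about reach and size.

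- **The 80% figure belongs to 128 participants and is correct; the attrition clause gives no number.** This stands as a limit on the finding: only adequate power after 25% loss is in question. It does not save the clause, because 80% is the sole criterion offered and 77.5% misses it.
- **The effect is small next to the uncertainty in f.** True. Detectable f moves from 0.25 to 0.258, while 0.25 is a generic medium value chosen because no data were available.
- **Covariate adjustment may recover the loss.** If f = 0.25 is taken on the unadjusted scale, a covariate–outcome correlation of about 0.25 brings power at 120 back to 80%. The article states no correlation, however, and its 128 takes no credit for one, so this shows that the gap is narrow and not that the clause is true.
- **The 113 is weaker evidence than it looks.** The article does not say that 113 is the number analysed for knowledge. A loss of 29.4% would also have defeated a correct 25% allowance: 172 × 0.706 ≈ 121, still below 128. Both remarks stand. The 113 illustrates the consequence and does not prove the error.
- **Readers can see 113 beside 128.** They can, in the abstract and in Results. That reduces the risk of being misled but does not correct the stated margin.

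**Conclusion.** The attrition clause is wrong as written. A target of 160 keeps the required 128 only up to 20% loss per group. At the 25% the plan names, 120 remain and power is 77.5%, about 2.6 points below the 80.1% at 128. The base requirement of 128 is sound.

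This rests on the article's own inputs (f = 0.25, two-sided .05, 1:1 allocation, complete cases) and on taking 80% as the meaning of sufficient power. The 75.0% at 113 needs one further assumption, that all 113 contribute to the knowledge analysis; if fewer do, power is lower. The shortfall is modest and changes no estimate or test, but the sentence gives a wrong margin for the primary analysis and should be corrected.

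**What to change.** Reword the attrition sentence in Sample Size and Power Calculation to say that 160 recruits (80 per group) keep 80% power for f = 0.25 with up to 20% loss in each group, and that at 25% loss (60 per group) power is about 77.5%. If the 25% allowance is to be mentioned as a planning figure, state that it would have needed 86 per group (172).

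Add that, with 113 participants, power for f = 0.25 is about 75%, and give the number actually analysed for knowledge, since the amount of data varies by measure. In the results paper, the confidence interval for the group difference should carry the interpretation of precision.

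The cost is a sentence or two and a slightly less favourable stated margin. Recruitment and analysis are complete, and no enrolment, data or analysis has to change.

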### Randomization and Group Allocation

This study aimed to recruit approximately 160 participants, with about 80 in each group. The study coordinator randomized participants into the intervention and control groups using a random number generator in R software, maintaining a 1:1 ratio for allocation to the experimental and control conditions. Participants in the intervention group first received the experimental condition, which included the psychotherapy training program after the baseline assessment. The waitlist control group received the control condition, meaning they participated in the psychotherapy training program only at the end of the study. The timeline of the study was as follows: all participants underwent a baseline assessment, the intervention group received the training program, and the control group received a control training program. After 8 weeks, all participants were followed up, and finally, the control group received the intervention training program (Figure 1).

### Recruitment

The researchers advertised the program online through the WeChat (Tencent Holdings Limited) official account of the Department of Psychiatry at Sir Run Run Shaw Hospital, Zhejiang University School of Medicine, to recruit potential participants. They encouraged sharing the program details with medical schools and hospitals. Interested individuals could register by sending messages and their identification to the research assistants ([name] and [name]). Research assistants then contacted the respondents to assess their eligibility, explain the study to each participant, and inform them about the allocation to either the control or intervention groups, where they would receive the psychotherapy training program.

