### Intervention

#### Control Group

After providing consent, participants allocated to the waitlist control group received a message encouraging them to complete all questionnaires from baseline through to the final follow-up at 8 weeks. They were sent messages via WeChat to thank them for their participation and to remind them of the timeline for completing the study. Once they finished the posttraining measurement, a digital booklet of the psychotherapy training program was provided to them via WeChat or as a hard copy upon request. After the trial concluded, participants in the control group were offered the opportunity to receive the psychotherapy training program free of charge.

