#### Intervention Group

All participants in the intervention group received the 2-day psychotherapy training program and were given a hard copy of the program booklet at recruitment. Additionally, supervision-based group meetings were held during the follow-ups at weeks 1, 2, 4, and 8, with each meeting lasting approximately 2 hours. During these follow-up meetings, instructors—including psychotherapists and psychiatrists—were available to answer any psychotherapy-related questions, encourage participants to practice psychological interventions, and provide further information to support the clinical application of psychotherapy.

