### Ethics Approval and Consent to Participate

This study was approved by the ethics committee of Sir Run Run Shaw Hospital, an affiliate of Zhejiang University School of Medicine (2024 Ethics Approval File No. 2024-0066). The trial was conducted in accordance with the Declaration of Helsinki. Participants were provided with informed consent before the baseline assessment. After thoroughly reading and understanding the content of the consent, they received a link to electronically sign their name at the end of the informed consent form and submit it via WeChat. Each participant was informed about the study’s purpose, procedures, measurements, potential risks, and benefits before recruitment. Informed consent was then obtained from each participant. Participation was entirely voluntary, and participants could withdraw from the study at any time. Coordinating researchers’ contact information was provided to all participants for any inquiries or concerns.

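### The stated order of eligibility, consent, randomization, disclosure and baseline contradicts itself and does not secure allocation concealment

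*Protocol article*

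**What the plan says.** All references are to the protocol article.

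- **Recruitment.** Research assistants contact people who respond to the advertisement "to assess their eligibility, explain the study to each participant, and inform them about the allocation to either the control or intervention groups". Consent is not mentioned in this sequence.
- **Randomization and Group Allocation.** A different role draws the allocation: "The study coordinator randomized participants into the intervention and control groups using a random number generator in R software". The arms are to be of equal size.
- **Intervention Group and Control Group.** Intervention participants "were given a hard copy of the program booklet at recruitment". For controls the timing differs: "Once they finished the posttraining measurement, a digital booklet of the psychotherapy training program was provided to them".
- **Abstract, Results.** "A total of 160 participants were recruited and randomized between January 4 and 12, 2024", and "Baseline assessments were conducted from January 28 to February 1, 2024". The main Results section repeats the January 4 to 12 dates for recruitment but does not date randomization.
- **Baseline and Posttraining Data Collection.** The text says that demographic data and questionnaires were gathered ahead of randomization.
- **Ethics Approval and Consent to Participate.** "Participants were provided with informed consent before the baseline assessment". The same section adds that people were told about the study before recruitment and that consent followed.
- **Textbox 1 and Table 1.** Willingness to be randomized and willingness to consent are entry criteria. Table 1 lists consent and eligibility above randomization, all ticked in one baseline column.

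**The concern.** The staff who assess eligibility are also the ones who tell respondents their arm, and an arm-specific item is handed out at recruitment. If the arm is known before enrolment is complete, two things can go wrong.

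First, entry can depend on the arm. A respondent assigned to wait has a reason to decline that a respondent offered the course does not. Participants are selected for interest in psychotherapy and every outcome is a self-rating, so differences in enthusiasm between arms could pass into the result. The ANCOVA adjusts for baseline knowledge and years of psychotherapy experience. It would not remove selection on enthusiasm beyond those two variables.

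Second, the self-rated baseline may be given with the arm known, and in the intervention arm with the booklet in hand. The knowledge questionnaire was built around the training program, and its baseline score is both a covariate and part of the change score that is the dependent variable.

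**Working it through.** The plan gives no figure on this point to reproduce. The check sets the statements side by side.

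**1. Dates.** Randomization closes January 12 and baseline opens January 28, so the shortest gap is 28 − 12 = 16 days. The longest runs from January 4 to February 1, which is 28 days. From randomization to the course on February 3 is 22 to 30 days.

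**2. Two orders follow from the text.**

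| Source | Implied order |
|---|---|
| Baseline data section with Ethics | consent → baseline → randomization |
| Abstract dates with Ethics | randomization (by January 12) → baseline (from January 28), with consent somewhere before baseline |

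Under the first order, consent precedes randomization and the baseline is blind to arm. Under the second, putting consent before baseline does not put it before randomization or disclosure. The two orders cannot both be true.

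**3. Which order the other statements fit.** An arm-specific booklet cannot be issued at recruitment unless the arm is known by then. Recruitment ended January 12, before any baseline date. Read literally, the booklet statement fits the second order and not the first. The rows of Table 1 also place randomization above the demographic and outcome assessments. If row order is taken as time order, it supports consent before randomization but also randomization before baseline.

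**4. Where consent sits relative to disclosure.** Ethics places consent after the information given ahead of recruitment. Recruitment mentions disclosure but not consent. Control Group speaks of people who had consented and were allocated, without ordering the two steps. No section explicitly places consent before the arm was revealed.

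**5. What a baseline given with the arm known would do.** With baseline as a covariate, analyzing change or the final score gives the same group coefficient. Apart from the term for years of experience, it is (difference in final means) − b × (difference in baseline means), where b is the within-arm slope of final on baseline score. If knowing the arm moves baseline ratings by a constant δ (intervention minus control), the estimate moves by −b × δ. The documents give neither b nor δ, and δ could have either sign.

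**6. Counts.** The Abstract reports 160 randomized, and 160 completed the baseline questionnaires. Taking the planned 80 per arm as denominators, 57/80 = 71.3% and 56/80 = 70.0% remained. The counts show no imbalance between arms. They cannot show who was screened out or declined before the 160 were fixed, because no such numbers are given by arm.

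**The case against.** A reader might infer that allocation was not concealed, that eligibility and disclosure happened in one contact, or that recruiters steered keen respondents into the intervention arm. The documents do not support any of these.

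- The Recruitment sentence lists tasks with disclosure last, and nothing says that they were done in one contact. It can also be read as telling respondents that they would be allocated to one of two groups. Disclosure to someone already eligible and consented does not breach concealment.
- A separate coordinator draws the allocation, and no section says that the assistants could see or predict it. Steering would require that.
- Screening on willingness to be randomized presupposes that the arm is not yet assigned. Ethics ties consent to recruitment as well as to baseline.
- Recruitment and randomization in the same nine days is equally consistent with one batch allocation at the end.
- A condensed article may leave the concealment mechanism to the full protocol, so its absence is no fault here.

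All of this stands, and it limits the point to what the stated order permits. It does not remove the point. The benign reading of the Recruitment sentence sits badly with a booklet issued to one arm at recruitment, and the clash between the Abstract dates and the baseline data section is a contradiction in stated text.

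**Conclusion.** The point holds in limited form. The stated order is contradictory and does not secure concealment. It permits respondents to complete enrolment, and to give the self-rated baseline used in the primary ANCOVA, knowing their arm. This rests on reading the Abstract dates and the booklet statement literally.

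Whether it happened is not shown, and no size of bias can be derived. A reader might try to put a number on it, for example by assuming that 8 of 80 per arm are selected on enthusiasm and differ by 1 to 2 SD, which gives 8/80 × 1 to 2 = 0.10 to 0.20 SD. Neither input comes from the documents, and the calculation ignores the covariate adjustment, so it should not be used.

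The Discussion admits that all measures are subjective and open to expectation, but does not mention possible knowledge of the arm at entry. The matter should be corrected.

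**What to change.** **As a plan.** Reconcile the Abstract, Recruitment, Randomization and Group Allocation, Baseline and Posttraining Data Collection, Intervention Group and Ethics sections around one order:

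1. Research assistants complete eligibility, signed consent and baseline for everyone, and the list is locked.
2. The coordinator, who takes no part in recruitment, makes one 1:1 allocation for the whole list.
3. Only then are arms disclosed and booklets issued.

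**For the trial as run.** The text must describe what was done. State when arms were disclosed relative to eligibility, consent and baseline, and correct whichever of the conflicting statements is wrong. Report any exclusions or refusals after disclosure, by arm. List knowledge of the arm at entry as a limitation if it occurred.

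**Cost.** The same steps and staff are used in a different order. The course starts for everyone on February 3, so batch allocation delays nobody's training. The downside is that participants learn their arm later. With baseline closing on February 1, they would have at most two days' notice of the course. Collecting baseline at enrolment and locking the list on January 12 would leave 22 days. For the completed trial the cost is a few sentences and, if the records exist, one row in the participant flow.
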